As such, reproductive experts have sought to clarify the best IVF treatment protocol for women with endometriosis. The administration of GnRH agonists prior to IVF/ICSI improves the pregnancy rate. The 2006 edition of the Cochrane guidelines recommend the use of 2–6 months of GnRH analogs before the initiation of an IVF cycle to “turn off the inflammatory response”, thereby increasing the pregnancy rate. One meta-analysis that included the randomized controlled trial (RCT) results comparing a general regimen with an ultra-long-acting regimen across three small-scale samples showed that the OR of the pregnancy rate was 4.28 (95% CIs = 2.00–9.15; [13]). Benschop did not find a difference in the pregnancy rates between GnRH agonists and GnRH antagonists administered prior to ART (OR = 0.81, 95% CIs = 0.26–2.54; 67 participants, one trial; [3]). Three additional reviews observed similar benefits for the oral administration of contraceptives versus no treatment [11]; these results require more corroborating evidence. In all cases, the quality of these trials was generally poor, and adequate allocation was concealed. These trials were also generally small, leading to imprecise findings, even when combined in a meta-analysis [4]. The conclusion of the most recent research was that long-term pituitary down-regulation has only a limited effect after including cryopreserved embryo transfers among women with severe endometriosis [16].

A typical ultra-long-acting regimen is to administer 2–3 doses of long-acting Triptorelin prior to ovulation induction to create a low estrogen status of menopause, which allows the ectopic endometrium to atrophy, and ovulation induction is then carried out by gonadotropin (Gn). However, although the patients with endometriosis who use this regimen for ovulation induction can achieve a certain pregnancy rate, the treatment cycle is long, the side effects of low estrogen (such as hectic fever, night sweating and loss of bone mass) are significant, and the use of gonadotropins is high. Therefore, how to ensure a good pregnancy rate while reducing the side effects during the treatment, the treatment cycle, the use of the treatment drug, and the treatment cost has become a focus of ovulation induction research for patients with endometriosis. Whether a briefer treatment interval is efficacious has not been studied [14]. No trials have compared a shorter interval with the typically long protocol.

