## Methods/design

### Aim

In this study, we hypothesis that that the efficacy of using one dose of long-acting GnRH agonist is no worse than that of two doses of GnRH agonist when carrying out IVF-assisted pregnancy for patients with combined endometriosis. At the same time, the treatment cycle is shortened and the total dose of Gn used is reduced.

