### Main research objective

Clinical pregnancy rate is no worse than that of a control group.

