### Data statistics

#### Sample size of participants

This study is a non-inferiority study; that is, it works well when the clinical pregnancy rate does not significantly differ between the two arms. A statistical expert calculated the trial’s sample size based on the existing average IVF cycle outcome across the three reproductive centers and the differences in the outcomes within the existing literature. A total of 401 women in each group will achieve 90% power to detect a non-inferiority marginal difference between group proportions of − 0.0500. The control group proportion is 0.6000. The treatment group proportion is assumed to be 0.5500 under the null hypothesis of inferiority. Power was computed for cases in which the actual treatment group proportion is 0.6500. The test statistic is the one-tailed Z-test (unpooled). The significance level of the test is targeted at 0.0500. The significance level actually achieved by this design is NA [12, 18]. Considering a dropout rate of 5%, we plan to recruit 842 women in total.

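### The 90% power assumes that one dose is 5 points better than two; if the two rates are equal at 60%, power is about 42%

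*Protocol article*

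**What the plan says.** The Aim of the protocol article puts forward that "the efficacy of using one dose of long-acting GnRH agonist is no worse than that of two doses of GnRH agonist". The Main research objective repeats this for the primary endpoint: "Clinical pregnancy rate is no worse than that of a control group". Neither claims an advantage for one dose.

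The section Sample size of participants describes success in similar terms: "This study is a non-inferiority study; that is, it works well when the clinical pregnancy rate does not significantly differ between the two arms". It then gives the calculation: "A total of 401 women in each group will achieve 90% power to detect a non-inferiority marginal difference between group proportions of" minus 0.05, with a control rate of 0.60, a one-dose rate of 0.55 under the null hypothesis, and a one-tailed unpooled Z-test at 0.05. The rate at which power was evaluated is stated openly: "Power was computed for cases in which the actual treatment group proportion is 0.6500".

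For the origin of these inputs, the section refers in general terms to average IVF outcomes at the three centres and to differences reported in the literature. The Background says of the shorter regimen: "Whether a briefer treatment interval is efficacious has not been studied".

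**The concern.** Power for a non-inferiority trial depends on the distance from the margin to the true difference assumed. With equal rates that distance is 5 points here. With one dose assumed 5 points better it is 10 points, and the required sample falls about four-fold. The objective and the description of success both point to similar rates as the case of interest, yet the only power figure given is for a clear advantage.

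A reader who takes the 90% at face value will think the trial is very likely to settle its question if the regimens perform alike. It is not. The risk is greater because the sample-size section equates success with the absence of a significant difference, and the Statistical analysis section plans between-group tests judged at p < 0.05. In a trial with low power at equality, a non-significant difference is easy to obtain and could be mistaken for evidence that one dose is no worse.

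**Working it through.** **Inputs, all from Sample size of participants:** control rate 0.60; margin 0.05; one-sided alpha 0.05 (z = 1.6449); power 90% (z = 1.2816); unpooled variance; one-dose rate under the alternative 0.65; 401 per arm.

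**1. Reproduce the stated sample size.**

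n = (z_alpha + z_beta)² × [pC(1 − pC) + pT(1 − pT)] / (pT − pC + margin)²

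n = (1.6449 + 1.2816)² × (0.24 + 0.2275) / (0.05 + 0.05)² = 8.564 × 0.4675 / 0.01 = 400.4, rounded up to 401. The stated figure reproduces.

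**2. Power at 401 per arm for other true one-dose rates.**

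Power = Phi[(pT − pC + 0.05) / SE − 1.6449], with SE = sqrt{[pC(1 − pC) + pT(1 − pT)] / 401}

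| True one-dose rate | SE | Distance to margin / SE | Power |
|---|---|---|---|
| 0.65 | 0.0341 | 0.10 / 0.0341 = 2.93 | 90.0% |
| 0.62 | 0.0344 | 0.07 / 0.0344 = 2.03 | 65.1% |
| 0.60 (equal) | 0.0346 | 0.05 / 0.0346 = 1.45 | 42.1% |
| 0.58 | 0.0347 | 0.03 / 0.0347 = 0.86 | 21.7% |

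Exact binomial enumeration of the same test gives 90.0% at 0.65 and 42.7% at 0.60, so the normal approximation is not the cause. If all 421 women recruited per arm were analysed, power at equality would be 43.5%.

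**3. What must be observed to declare non-inferiority.**

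The lower one-sided 95% bound must exceed −0.05, so the observed difference must exceed 1.6449 × SE − 0.05. With both rates near 0.60 this is 1.6449 × 0.0346 − 0.05 = 0.0569 − 0.05 = 0.0069. One dose would have to be observed about 0.7 points above two doses. An exact tie would fail.

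**4. Scale of the dependence on 0.65.**

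For 90% power at equal rates: n = 8.564 × 0.48 / 0.05² = 1,644.3, that is 1,645 per arm against 401, a ratio of about 4.1. This shows how much rests on the assumed advantage; it is not a proposal to enlarge the trial.

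**The case against.** The strongest reply is that nothing is hidden or miscalculated. Control rate, null rate, alternative, test and alpha are all printed, and 401 follows from them. That stands: a reader might infer an arithmetic error or a concealed assumption, and the document supports neither.

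A second reply is that no worse covers every true rate above the margin, including 65%, and that a non-inferiority trial may be planned on an expected advantage. This also stands in part. The document sets no numeric alternative of equality; that is an inference from its objective and its description of success. But planning on an advantage needs a reason, and none specific to 0.65 is given.

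Third, it would go too far to say that nothing supports 0.65. The section does refer to centre data and literature, and a condensed article need not print them. The supportable statement is that no specific justification appears in the text shown. Nor does the Background establish that a shorter course should do worse. It cites a recommendation of 2–6 months of treatment to raise pregnancy rates, but also recent work finding only a limited effect of long down-regulation in severe disease. The direction is left uncertain, and a 5-point gain is not supported either.

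Finally, a reader might add the dropout allowance to the charge: "Considering a dropout rate of 5%, we plan to recruit 842 women in total". This total comes from 401 × 1.05 = 421 per arm; dividing by 0.95 gives 423 per arm, 846 in total. The difference is 4 women. A 5% loss from 842 leaves about 400 per arm, with power 89.98% instead of 90.0% at the design alternative. It is immaterial and forms no part of this point.

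**Conclusion.** The point holds as a planning assumption at odds with the trial's objective, not as a calculation error. The 90% is correct only for a true one-dose rate of 65% against 60%. If both rates are 60%, the natural planning case for a no-worse question, power is about 42%, and the trial would fail to show non-inferiority about 58% of the time. At a one-dose rate of 62%, power is about 65%.

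These figures rest on the document's own control rate, margin, one-sided alpha and test, with 401 evaluable women per arm. Only the true one-dose rate is varied. They do not show that 65% is wrong; they show that the headline power depends on it and that the text does not say why it was chosen.

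**What to change.** Leave the sample size as it is and restate the power in Sample size of participants:

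- say that 90% power applies only if the true one-dose rate is 65%;
- give the specific basis for 65%, by naming the centre data or the published differences used;
- report power of about 42% if both rates are 60%, and preferably about 65% at a one-dose rate of 62%;
- replace the sentence equating success with no significant difference by a statement that non-inferiority is judged against the 0.05 margin, and that neither a failure to show it nor a non-significant difference will be read as no worse or as equivalence.

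Possible wording:

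> With 401 evaluable women per arm, power to show non-inferiority at a margin of 5 points is 90% if the true one-dose rate is 65% [basis to be given] and about 42% if both rates are 60%. A result that does not show non-inferiority will be reported as inconclusive unless the confidence interval supports a stronger statement; a non-significant difference will not be taken as evidence of non-inferiority or equivalence.

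The cost is a few sentences, the work of documenting the source of 65%, and a less favourable power figure on record. No additional women are needed.

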#### Statistical analysis

Statistics will be treated rigorously according to the following steps:

Step 1: Summary of research data

Baseline characteristics and pregnancy results will be summarized, such as number of participants, withdrawal rate. For continuous variables (such as age, FSH level, the number of Gn days, and total Gn dose), mean and standard error will be shown, if the distribution is asymmetric, then median and quartile will be determined. For categoricalvariables (such as clinical pregnancy outcomes), percentage of different groups will be displayed.

Step 2: Comparison between groups

Chi-square test, fisher’s exact test, Mann-Whitney U testor the Kruskal-Wallis test will be usedto determine whether differences in the results of two groups have statistical significance (*p* value < 0.05). Subgroup analysis will be performed according to different degrees of patient’s endometriosis. Endometriosis will be divided into mild degree (grades I and II) and severe degree (grades III and IV) due to the concern of false negatives and false positives.

Step 3: Multivariable analysis and sensitivity analysis

If the baseline data are not balanced between the two groups after randomization, we will adjust the unbalanced factors and perform a multivariable analysis. We will perform sensitivity analysis for loss of follow-up, missing data, which may bias experimental results.

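### The severity subgroup analysis is tied only to p<0.05 difference tests, which, if applied within each severity class, cannot show whether the treatment effect differs by severity

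*Protocol article*

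**What the plan says.** All references are to the protocol article.

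- **Statistical analysis, Step 2 (Comparison between groups).** Chi-square, Fisher's exact, Mann-Whitney or Kruskal-Wallis tests are to show "whether differences in the results of two groups have statistical significance", with p<0.05 as the criterion. The next sentence adds: "Subgroup analysis will be performed according to different degrees" of endometriosis. Four grades are then merged into two classes, I-II and III-IV, "due to the concern of false negatives and false positives".
- **Statistical analysis, Step 3.** A multivariable analysis is planned only if baseline factors turn out unbalanced. It is not linked to the subgroup question.
- **Sample size of participants.** The trial is a non-inferiority trial: "A total of 401 women in each group will achieve 90% power to detect a non-inferiority marginal difference between group proportions of" minus 0.05. "The control group proportion is 0.6000", and "Power was computed for cases in which the actual treatment group proportion is 0.6500". After 5% dropout the total is 842, or 421 per arm.
- **Grouping method.** Disease is scored and its degree recorded at grouping, so severity is a baseline factor. The expected share of women in each class is not given.

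**The concern.** The subgroup sentence sits in a step whose only methods are two-group difference tests. Followed as written, the step most naturally yields one p-value for mild disease and one for severe disease. A significant result in one class and a non-significant result in the other is not evidence that the effect differs between them. That question needs the difference between the two class-specific effects, with its own standard error.

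Merging grades reduces the number of tests and enlarges each class. It does not supply that comparison, so the safeguard does not match the error that the text says it is worried about.

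A split result would invite interpretation. The Background reports lower pregnancy rates in severe than in mild disease (odds ratio 0.60). The sample-size section also describes success as the absence of a significant difference between arms. Carried into a smaller class, that idea makes a favourable verdict easier to reach, because power is lower there.

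**Working it through.** **Inputs.** From Sample size of participants: control rate 0.60, planning rate 0.65, margin 0.05, one-sided alpha 0.05, power 90%, 401 per arm before and 421 after dropout. From Step 2: p<0.05, taken as two-sided because the number of sides is not stated. Assumed: a 50/50 severity split, about 210 per arm per class; splits of 30/70 and 20/80 are also shown.

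**The plan's own figure.** The unpooled standard error with 401 per arm is √[(0.60×0.40 + 0.65×0.35)/401] = √(0.4675/401) = 0.0341. Power is Φ(0.10/0.0341 − 1.645) = 0.900. The 401 reproduces.

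**Separate tests, same true effect in both classes.** For class size n per arm and treatment rate p, SE = √[(0.24 + p(1−p))/n] and δ = (p − 0.60)/SE. The chance of significance is π = Φ(δ − 1.96) + Φ(−δ − 1.96). The classes are independent, so P(exactly one significant) = π₁(1 − π₂) + π₂(1 − π₁), which is 2π(1 − π) at 50/50.

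| True rates (shorter regimen vs control) | SE, n=210 | δ | π per class | Exactly one significant, 50/50 | 30/70 | 20/80 |
|---|---|---|---|---|---|---|
| 0.60 vs 0.60 | 0.0478 | 0 | 0.050 | 9.5% | 9.5% | 9.5% |
| 0.65 vs 0.60 | 0.0472 | 1.06 | 0.185 | 30% | 31% | 32% |
| 0.55 vs 0.60 | 0.0482 | −1.04 | 0.180 | 29% | 30% | 31% |
| 0.50 vs 0.60 | 0.0483 | −2.07 | 0.544 | 50% | 55% | 62% |

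With no arm difference, at least one class is significant in 1 − 0.95² = 9.75% of trials. Using 401 rather than 421 per arm changes the 50/50 column by no more than about one point.

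**What an interaction test would do.** At two-sided 0.05 it holds a false claim of a severity difference at 5%. To illustrate its power, take 0.60 vs 0.60 in one class and 0.50 vs 0.60 in the other. The SE of the difference in risk differences is √[(0.48 + 0.49)/210] = 0.068, and power is Φ(0.10/0.068 − 1.96) ≈ 0.31. With 401 per arm, power is about 11%, 30%, 58% and 82% for true differences in effect of 5, 10, 15 and 20 points.

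**The case against.** **Separate testing is not written down.** This stands. The article names the subgroup and its levels but not a within-class method. A reader might infer that separate tests are prescribed; that rests on where the sentence is placed and must be presented as an inference.

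**The interaction model may be in a statistical analysis plan that is not shown.** This is fair, and the absence of an interaction term alone would be no finding. What remains is what the article does fix: difference tests at p<0.05, and a merging of grades offered as the answer to false positives and negatives, which cannot tell whether the effect differs.

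**Chance will not often split the classes.** This largely stands. With no arm difference the rate is 9.5%, and exactly one class is significantly worse in only 2×0.025×0.975 = 4.9% of trials. At the planned 65% versus 60%, nearly all of the roughly 30% consists of one class significantly better and the other not significant, so neither would look unsuitable. The 50% figure needs a 10-point loss, twice the margin.

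**A reader might apply the non-inferiority rule within each class and get higher rates of disagreement.** The document states that rule only for the whole trial, so such figures would describe a procedure that nobody has proposed.

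**The Background does not say that severe disease responds differently from mild.** This is correct. It reports a limited effect of long-term down-regulation in severe disease without a comparison with mild disease. Only the lower pregnancy rate is supported.

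**Conclusion.** The point holds in a limited form. The only method and the only safeguard stated for the severity subgroup do not address whether the effect varies by severity. Under the natural reading, exactly one class would be significant in 9.5% of trials with no arm difference, about 30% with a common 5-point effect and about 50% with a common 10-point loss.

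These figures rest on an assumed 50/50 split, two-sided tests, the normal approximation, 421 per arm, and the reading that the arms are tested separately. The document does not support an unqualified statement that chance will often make the regimen look suitable for one severity and not the other.

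This is a secondary analysis. The sample size and the primary conclusion are unaffected. The change is worth making because it is cheap.

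**What to change.** Replace the subgroup wording in Step 2 with a sentence to this effect: clinical pregnancy will be analysed in one model containing treatment, severity (grades I-II versus III-IV) and their interaction. The interaction estimate with its confidence interval, and the risk difference with confidence interval in each class, will be reported. The analysis is exploratory, and no claim of non-inferiority or inferiority will be made within a class. Expressing the interaction as a difference in risk differences keeps it on the scale of the margin.

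The cost is wording only, since severity is already scored and recorded at grouping. The downside is low power, about 30% for a 10-point difference in effect. The usual result will be no evidence of a difference, and that should not be reported as evidence that the effect is the same in both classes.

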Compared with women with tubal infertility, women with endometriosis have lower IVF/ICSI success rates. One meta-analysis that included 22 non-randomized controls reported that the infertility of women with endometriosis was lower than that of those with tubal infertility (odds ratio [OR] = 0.56, 95% confidence intervals [CIs] = 0.44–0.7; [1]). A multivariate analysis also showed that the fertilization and implantation rates of women with endometriosis were significantly lower than those of women receiving the same number of eggs. The low rates of pregnancy and implantation are primarily due to poor egg quality. Poor egg quality leads to a low fertilization rate, which in turn affects the quality of the embryo and affects the implantation rate, especially in patients with severe endometriosis. In oocyte donation cycles, when healthy women donate their disease-free eggs to women with endometriosis, the recipient is associated with comparative endometrial receptivity and pregnancy rates. When the oocytes of women with endometriosis are donated to disease-free women, their implantation rates are lower [6]. Severe endometriosis is associated with a lower pregnancy rate than mild endometriosis (OR = 0.60, 95% CIs = 0.42–0.87; [1]). A meta-analysis provided statistical evidence of the above statement, finding relative pregnancy rates of 0.93 (95% CIs = 0.87–0.99) and 0.79 (96% CIs = 0.69–0.91) among women with mild and severe endometriosis, respectively, through IVF [10].

No clear mechanism has been defined to explain the relationship between endometriosis and subfertility. The complex mechanisms of ovulation, fertilization, tubal pick-up oocyte, and the transport of the embryos or embryo implantation might be partially influenced by hormones [5]. Elevated cytokine and progesterone concentrations in the follicular fluid were found in women with endometriosis [7]. This theory is supported by findings showing concentrations of prostaglandins, proteases, and inflammatory cytokines in the peritoneal fluid of women with endometriosis [2].

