### Grouping method

Center controlled grouping will be performed. After entering the IVF/ICSI cycle and establishing medical records, the researchers at each center will screen for patients who meet the enrollment requirements according to the inclusion and exclusion criteria. Patients with endometriosis will be scored, and the degree of endometriosis (mild, moderate or severe) will be evaluated and recorded in a Microsoft Excel spreadsheet for each center. At the same time, the researchers at the center will be contacted, and the statisticians at the center will group the patients according to the number randomly generated by Excel or contact the central office.

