### Study steps and observation parameters

#### Study steps

##### Visit 1

Screen for subjects based on inclusion/exclusion criteria;

Explain the study to the subjects and have the subjects sign the informed consent form;

Collect medical history and demographic information and perform routine physical examination (including height and weight) and pelvic examination;

Count antral follicles;

Baseline anti-Müllerian hormone (AMH), FSH, LH, E2, testosterone (T), P, and prolactin (PRL) levels in serum.

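### Step 3 chooses adjustment covariates by an undefined baseline imbalance instead of naming prognostic factors in advance, and does not say whether the adjusted or the unadjusted result decides non-inferiority

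*Protocol article*

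**What the plan says.** The between-group comparison comes first, in Step 2 of the Statistical analysis section. It lists tests without covariates ("Chi-square test, fisher’s exact test, Mann-Whitney U" and the Kruskal-Wallis test) and attaches no condition to them. This fits the sample size section, which is built on a one-tailed unpooled Z-test of two proportions with a margin of -0.05.

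Step 3, which covers multivariable and sensitivity analyses, then adds: "If the baseline data are not balanced between the two groups after randomization, we will adjust the unbalanced factors and perform a multivariable analysis". So the protocol fixes both the trigger (observed imbalance) and the covariate set (whatever turned out unbalanced).

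Severity appears in Step 2 as a subgroup factor ("Subgroup analysis will be performed according to different degrees of" disease, grouped as grades I-II and III-IV). It is known before allocation: under Grouping method, "the degree of endometriosis (mild, moderate or severe) will be evaluated and recorded". The Background calls it prognostic: "Severe endometriosis is associated with a lower pregnancy rate than mild endometriosis", with an odds ratio of 0.60 (95% CI 0.42-0.87).

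Other candidate covariates are collected at Visit 1: "Count antral follicles" and "Baseline anti-Müllerian hormone (AMH), FSH, LH, E2, testosterone (T), P, and prolactin (PRL) levels in serum". Centre features in the allocation ("Center controlled grouping will be performed").

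**The concern.** Whether to adjust for a baseline factor should depend on whether it predicts pregnancy. How far the arms happen to differ on it is a separate matter, and in a properly randomised trial such differences arise by chance. A rule driven by observed difference can put a hormone level of no prognostic value into the model because it differed by luck. It can equally leave out severity because severity happened to look even, and then the precision that severity offers is lost.

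The rule is also open to interpretation. What counts as unbalanced is not defined, so two analysts following the same text could fit different models, and the choice would be made with trial data in view. If the adjusted and unadjusted results fell on opposite sides of -0.05, the protocol would not say which one to believe. This is a rule that the protocol states, not a detail left for later. An analysis plan that followed the sentence faithfully would inherit the problem.

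**Working it through.** **1. The plan's own figure.** Inputs from the sample size section: control rate 0.60, true treatment rate 0.65, margin 0.05, one-sided alpha 0.05, power 0.90, unpooled variance.

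n per arm = (1.645 + 1.282)² × (0.60×0.40 + 0.65×0.35) / (0.65 - 0.60 + 0.05)² = 8.564 × 0.4675 / 0.01 = 400.4, rounded up to **401**.

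Power at 401: SE = √(0.4675/401) = 0.0341; 0.10/0.0341 - 1.645 = 1.284, giving 0.9004. With 5% added, 401 × 1.05 = 421 per arm, 842 in total. The stated size is reproduced, and it comes from an unadjusted test.

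**2. How often chance alone would trigger adjustment.** The protocol gives no criterion, so two assumptions are needed: imbalance is judged at p<0.05, and the factors are independent. Then P(at least one) = 1 - 0.95^k. Visit 1 gives seven serum hormones and the antral follicle count (8 factors). Age and severity make 10, height and weight make 12.

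| Factors k | 1 - 0.95^k |
|---|---|
| 5 | 0.226 |
| 8 | 0.337 |
| 10 | 0.401 |
| 12 | 0.460 |

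Some of these factors are likely to be correlated (for example AMH, antral follicle count, FSH and age). Positive dependence would lower the figures.

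**3. What the rule does to error and power.** Simulation with 401 per arm, ten independent binary baseline factors of which three are prognostic, a linear probability model with robust standard errors, and 8,000 runs per scenario. The null was 0.55 versus 0.60 and the alternative 0.65 versus 0.60. The total R-squared of the prognostic factors is assumed, because the protocol gives none.

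| R-squared | Quantity | Unadjusted | Balance-triggered | Fixed adjustment | Better of unadjusted and triggered |
|---|---|---|---|---|---|
| 0.02 | Type I error | 0.048 | 0.047 | 0.050 | 0.051 |
| 0.05 | Type I error | 0.054 | 0.053 | 0.055 | 0.056 |
| 0.10 | Type I error | 0.048 | 0.044 | 0.043 | 0.051 |
| 0.02 | Power | 0.901 | 0.901 | 0.905 | – |
| 0.05 | Power | 0.899 | 0.898 | 0.911 | – |
| 0.10 | Power | 0.898 | 0.901 | 0.921 | – |

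The simulation error of a type I error entry is about √(0.05×0.95/8000) = 0.0024, and of a power entry about √(0.90×0.10/8000) = 0.0034. The rule applied mechanically stays near 0.05, and so does picking the more favourable of the two results. Fixed adjustment gains 0.4, 1.2 and 2.0 points of power over the triggered rule (0.9045 - 0.9005, 0.9105 - 0.8981, 0.9208 - 0.9006). The triggered rule gains essentially nothing over no adjustment.

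**The case against.** The strongest reply is that Step 3 is supplementary. Step 2 compares the arms without adjustment and without condition, the sample size rests on an unadjusted Z-test, and the adjustment sentence sits beside the sensitivity analyses. An unadjusted risk difference is a valid primary analysis in a randomised trial. All of this stands. A reader might infer that the primary test itself is picked from the data, but the document does not say so. What it leaves open is which result takes precedence, and that gap remains on either reading.

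Several other strong readings also fail:

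- **Severity is ignored.** It is not, because Step 2 plans a subgroup analysis by grade. That analysis does not adjust the main comparison, but it is a use of the factor.
- **The absence of a centre term is a fault in itself.** An article may leave that to the full protocol or analysis plan. Centre belongs in the fix as an obvious candidate, not in the charge.
- **An odds ratio would be set against a risk-difference margin.** No model type or effect measure is named for the multivariable analysis, so this cannot be charged. The most that can be said is that the scale should be stated.
- **Four trials in ten would change model for no reason.** The 40% depends on an assumed p<0.05 trigger and ten independent factors. Step 1 speaks only of summarising baseline data, and the p<0.05 in Step 2 refers to results.

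It is also fair to say that the measured harm is small.

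**Conclusion.** The point holds in a limited form. Step 3 states a covariate rule that rests on chance imbalance and not on prognostic value. It defines no criterion for imbalance and leaves unsaid whether the adjusted or unadjusted result decides non-inferiority.

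The consequences are analyst discretion and some forgone precision: about 0.4 to 2 points of power at the planned size, if the named factors explain 2% to 10% of the outcome variance. The lowest of these gains is close to simulation error. A reader might infer a false-positive problem, but the calculations do not support one. One-sided error was 0.044-0.053 under the rule and 0.051-0.056 when the more favourable result was taken. The trigger frequencies (23%, 40% and 46% for 5, 10 and 12 factors) illustrate how easily the rule could fire and are conditional on the assumptions given with them. The point is worth correcting because the correction is cheap, but it does not undermine the trial.

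**What to change.** Delete the balance trigger and replace the sentence in Step 3 with text to this effect:

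> The difference in clinical pregnancy rate will be estimated with adjustment, in every case, for centre, endometriosis grade (I-II versus III-IV), age, and antral follicle count [or AMH; choose one now]. The result will be expressed as a risk difference, and its confidence limit, at the level of the planned one-sided test, compared with -0.05. The [adjusted / unadjusted] risk difference is primary; the other is a sensitivity analysis. Baseline balance will be described but will not alter the model.

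The sponsor should settle the bracketed choices before outcomes are examined by arm. Either estimate can be primary. The unadjusted one matches the test used for the sample size, and the adjusted one is somewhat more precise. If a logistic model is used, its result should be standardised to a risk difference.

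The cost is a change of wording and a slightly more complex model than the Z-test. The planned size stays at 842. No new data are needed: centre is known for every patient, severity is recorded at grouping, and the remaining factors come from the Visit 1 assessments. Severity is recorded there as mild, moderate or severe, so the mapping to grades I-II and III-IV should be written down.
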